# LONG-TERM FOLLOW-UP

There will be an opportunity for inclusion in a long-term follow-up, where participants from both the randomized controlled study and the cohort study will be eligible if they consent. In the long-term follow-up, conducted 10 years post-inclusion, we will utilize the unique Swedish personal identification number and gather data after study conclusion on infertility treatments from the National Register of ART in Sweden (Q-IVF) live births from the Swedish Medical Birth Register (MFR) and The National Pregnancy Register and number of recurrent endometriosis surgeries from Gynop. For details about variables collected from each register see appendix.

# THE REPRODUCTIVE OUTCOMES RELATED TO P-PROGESTERONE ON THE DAY OF TRANSFER OF THE CRYOPRESERVED EMBRYO WITH HORMONE REPLACEMENT THERAPY-CYCLES

Patients suffering of endometriosis may differ in their response to exogenous progesterone when undergoing frozen embryo transfer cycles(FET) with standard hormone replacement therapy, HRT (44). The aim of this observational sub-study is to investigate possible association between P- progesterone levels on the day of FET in patients with endometriosis undergoing HRT cycles and their reproductive outcomes. Primary outcome will be live birth rate and secondary outcomes will include clinical pregnancy rate and miscarriage rate. Potential difference in P-progesterone levels between the two different study groups (surgery first vs IVF first) will also be investigated.

Blood samples to analyze P-progesterone will be collected on the day of FET, and the test result will be recorded in the eCRF, as a sub-group analysis. The subgroup analysis includes only HRT-FET cycles in patients with endometriosis AAGL stage III-IV diagnosed by either ultrasound or surgery. The standard HRT protocol for endometrial preparation is usually performed by using Progynon (4-8 mg/d) per os with the start on the first, second or third day of menstruation with a possible addition of transdermal estrogen according to local routine. Cyclogest (400 mg/12 h) or other vaginal progesterone preparation of similar efficacy should be commenced when the endometrium is regarded as appropriate by the treating physician (as a rule 7 mm or thicker). Blastocyst transfer should be scheduled on the sixth day of progesterone supplementation (45).

# STATISTICAL CONSIDERATIONS

The primary exposure is the randomized allocation (surgery prior to ART vs ART alone). All analyses will follow the intention-to-treat (ITT) principle, meaning participants are analyzed according to their randomized group regardless of adherence. Per-protocol and as-treated analyses will be conducted as sensitivity analyses to assess robustness. An interim analysis at the halfway point is planned to monitor potential adverse effects and ensure the safety of the interventions.

No formal adjustment for multiplicity will be made; the primary endpoint will be tested at a two-sided α=0.05, while secondary endpoints are considered supportive and exploratory. Sensitivity analyses will address protocol deviations, handling of missing data, and robustness to alternative modelling approaches.

DATA ANALYSES

Baseline demographic and patient’s characteristics will be summarized by treatment group. Continuous variables will be described with mean, standard deviation, median, interquartile range, minimum and maximum, and categorical variables with counts and percentages.

Primary endpoint

The primary endpoint of the study is the Cumulative Live Birth Rate (CLBR), defined as the proportion of participants achieving at least one live birth within three years following the initiation of treatment.

**Primary analysis**

The primary analysis will compare proportions between treatment groups and report the crude relative risk (RR) with 95% confidence intervals. Adjusted analyses will use log-binomial regression (or modified Poisson with robust variance if convergence fails), including prespecified covariates (age, BMI, AMH, ART type, center). A two-sided α=0.05 will be used.

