# WHY THIS TRIAL IS NEEDED

BACKGROUND

Endometriosis

Endometriosis is a prevalent condition affecting 10% of female population of reproductive age, leading to pain and subfertility (1). An earlier systematic literature review and meta-analysis suggests that women with advanced endometriosis (revised American Society for Reproductive Medicine classification of endometriosis (rASRM) stage III-IV) have a lower likelihood of achieving clinical pregnancy/live birth compared to women without endometriosis, while this difference has not been observed for mild disease (stage I-II) (2).

Gynecological Ultrasound and staging

The prevalence of endometrioma and deep endometriosis found through systematic transvaginal ultrasound on women referred for ART treatment in Sweden has been estimated at 21.8% (3). Additionally, 75.8% of those with endometriosis were unaware of their condition prior to diagnosis (3). In recent years, two staging systems, namely the American Association of Gynecologic Laparoscopists (AAGL) Endometriosis classification (4, 5) and #ENZIAN (6) have gained prominence owing to their accuracy when juxtaposed with surgical findings.

Surgical Treatment

Women with endometriosis seem to experience pain relief after bowel surgery due to endometriosis (7, 8). Consensus from the European Society of Human Reproduction and Embryology (ESHRE) indicates that surgery can be performed prior to treatment with assisted reproductive technologies (ART) (7). Additionally, the number of spontaneous pregnancies is high after surgery on patients with deep endometriosis (10). Furthermore, in patients with endometriosis stage I-II or in infertile patients with endometriomas, surgery can in some cases be considered to improve fertility (7-9). However, the risk of severe complications in patients undergoing rectal surgery is up to 10% including anastomosis leakage and fistulas (10, 11).

Fertility treatment

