Cumulative live-birth rate within three years from first treatment (surgery or ART treatment).

Definition of primary outcome measure

CLBR is defined as any live births from first treatment until end of follow up (three years from first ART treatment or surgery or drop out from the study, whichever comes first).

Primary outcome will be calculated considering also the following pre-specified subgroups: study center,  type of ART-treatment (IVF or ICSI), age (< and > 35 years), ovarian reserve ( anti-mullerian hormone (AMH) <0.5ng/L, 0.5-3.5 ng/L and AMH >3.5ng/L ) (35) adnexal surgery (yes/no), surgery on deep endometriosis anterior compartment (yes/no) or deep endometriosis posterior compartment (yes/no) (defined by Classification of surgery, “Klassifikation av vårdåtgärder” (KVÅ codes), see appendix).

SECONDARY OUTCOME MEASURE

- Cumulative Pregnancy Rate (CPR)
- Time to pregnancy and live birth
- Spontaneous Pregnancy Rate
- Miscarriage rate and/or extrauterine pregnancies
- Reproductive outcomes per IVF cycle
- Rate of recurrent implantation failure (RIF), (20) evaluated at the end of the study period
- Infections after oocyte pick-up
- Quality of life and pain
- Peri- and two months postoperative complications classified by Clavien-Dindo and Classic systems
- Health care costs
- Obstetrical outcomes and complications
- P-progesterone levels on day of embryo transfer at first HRT frozen-thawed artificial embryo transfer cycle

Definition of secondary outcome measures

Cumulative Pregnancy Rate (CPR) is defined as all pregnancies confirmed with ultrasound, from first treatment (surgery or ART) until three years of follow up.

Time to pregnancy is defined as time from first treatment (surgery or ART) to first pregnancy confirmed with ultrasound. Time to live birth defined as time from first treatment (surgery or ART) to first livebirth.

Spontaneous pregnancy rate is defined as any spontaneous pregnancy occurring between first treatment and end of follow-up.

Miscarriage rate defined as frequency and proportion of spontaneous loss of any clinical and biochemical pregnancy before week 22 and/or extrauterine pregnancy defined as a pregnancy not located in the uterine cavity, occurring between first treatment and end of follow-up.

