*Assisted reproductive technologies data (for each IVF/ICSI-cycle, max 3):*

- Complication – yes/no
- Type of complication (infection, ovarian hyperstimulation syndrome (OHSS), bleeding)
- Time from surgery to first oocyte pick-up
- Type of IVF protocols (GnRH agonist protocol/GnRH antagonist protocol)
- Total dose/mean daily dose of follicle stimulating hormone (rFSH) /human menopausal gonadotropin (hMG)
- Duration of IVF stimulation (days)
- Cancelled cycle (before or after oocyte pick up (OPU)) (excluding freeze all cycles)
- Reason of cancelled cycle
- Type of ovulation triggering [GnRH agonist (Gonapeptyl/Suprecur/Suprefact/Synarela) / Ovitrelle]
- Date of OPU
- Freeze all cycle (yes/no) and reason of that
- Number of retrieved oocytes (GV/MI/MII)
- Performed fertilisation method (ICSI/IVF)
- Sperm – fresh vs frozen
- Donor sperm – yes/no
- Origin of sperm – ejaculated/ epidydimal / testicular
- Oocytes – fresh vs frozen
- Number of inseminated oocytes
- Number of fertilised oocytes
- Number of good quality embryos defined according to Gardner criteria as AA, AB and BB for blastocysts (23) or top and good quality based on the number of blastomeres, the fragmentation rate and the multinucleation of blastomeres for cleavage stage embryos (24).
- Number of frozen blastocysts (D5 or D6)
- Date for fresh embryo transfer
- Embryo age at fresh embryo transfer (D2, D3, D4, D5 or D6)
- Number of embryos transferred (SET/DET)
- Type of embryo transfer (Fresh/Frozen)
- Type of protocols for Frozen-thawed ET (Natural Cycle (NC), HRT, Letrozol-stimulated, gonadotropinstimulated)
- Use of GnRH downregulation in Frozen-thawed HRT cycle (yes/no, number of days)
- Total estrogen dose and type of estrogen preparations in HRT FET-cycle
- Endometrial thickness prior to embryo transfer in HRT-FET
- Cycle day of endometrial thickness measurement in HRT-FET
- P progesterone level on the day of ET in HRT-FET
- Date of frozen ET
- Urinary pregnancy test (positive/negative)
- Gestational age at pregnancy ultrasound
- Fetal heartbeat at ultrasound (present/absent)
- Number of foetuses
- Number of gestational sacs
- Result foetus 1 (miscarriage, abortion, ectopic pregnancy, delivery)
- Date for delivery / end of pregnancy foetus 1
- Result foetus 2 (miscarriage, abortion, ectopic pregnancy, delivery)
- Date for delivery / end of pregnancy foetus 2
- Result foetus 3 (miscarriage, abortion, ectopic pregnancy, delivery)
- Date for delivery / end of pregnancy foetus 3

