**Exploratory subgroup analyses**

Exploratory subgroup analyses will be conducted using treatment-by-subgroup interaction terms in regression models. Subgroups of interest include type of ART (IVF vs ICSI), age (<35 vs ≥35 years), ovarian reserve (AMH categories), and surgical characteristics (adnexal surgery yes/no; anterior vs posterior deep endometriosis, KVÅ codes). These analyses are exploratory and not adjusted for multiplicity.

Secondary endpoints

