**Additional analysis**

– Exploratory subgroup analyses will not be adjusted for multiplicity.

– Safety outcomes will be summarized descriptively by treatment group (frequency, severity, relation to treatment).
– All available data will be used, including outliers.
– Missing outcome data will be handled under the missing-at-random assumption via maximum likelihood in mixed models; for regression models requiring complete covariates, complete-case analysis will be applied.

Covariates

Primary and secondary outcomes will be adjusted for prespecified covariates (age, BMI, AMH, ART type, center), chosen based on clinical relevance and prior evidence.

POWER CALCULATION AND SAMPLE SIZE

The sample size calculation was based on a two-sample comparison of proportions with a two-sided α=0.05 and 80% power. Based on observational data (18, 19), the cumulative live birth rate (CLBR) after three IVF cycles was assumed to be 55% in the ART-only group and 71% in the surgery+ART group (relative risk ≈1.29). This yields a required sample size of 142 participants per arm (284 total). Allowing for 20% attrition, the planned total sample size is 350 participants.

The necessary sample size for this study is estimated to 323 patients to accommodate a statistical analysis method. This estimation uses the 'pwr' package in R, specifically employing the power.prop.test method, which is designed to compare two proportions. This method is more aligned with contemporary statistical practices and provides a clear, transparent methodology for determining the required sample size based on expected success rates.

This means inclusion of 29 patients from/each center/year and 15 surgeries/year. In a Swedish study published in 2022 the prevalence of endometriosis in patients referred for ART-treatment was 21.8% and 17.2% of women had DE (14). In 2021 almost 10 500 IVF cycles were performed in Sweden, while more than 5 500 of those were first-time IVF/ICSI with autologous gametes ((46) Figure 22).

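### The adjusted models and one primary-outcome subgroup condition on IVF versus ICSI, which is recorded after randomisation and has no value for some women, including some with a live birth

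*Protocol*

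**What the plan says.** All references are to the protocol.

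- **Primary analysis** (Statistical Considerations). The arms are compared as proportions, and the trial will "report the crude relative risk (RR) with 95% confidence intervals". Adjusted log-binomial or modified Poisson models follow, "including prespecified covariates (age, BMI, AMH, ART type, center").
- **Covariates** (under Additional analysis). The list is extended: "Primary and secondary outcomes will be adjusted for prespecified covariates (age, BMI, AMH, ART type, center"). The Cox models under Time-to-Event outcomes also refer to the prespecified covariates.
- **Meaning of ART type.** Study Objectives, in defining the primary outcome, names "type of ART-treatment (IVF or ICSI") as a subgroup. Exploratory subgroup analyses repeats it: "Subgroups of interest include type of ART (IVF vs ICSI").
- **Where it is recorded.** The baseline characteristics contain no IVF/ICSI item. The participant-level record is "Performed fertilisation method (ICSI/IVF"), held in the ART data for each cycle, up to three.
- **What counts as an event.** The primary outcome counts every live birth from first treatment, with no restriction on how the pregnancy arose. Spontaneous pregnancy is a secondary outcome, and the background states that "the number of spontaneous pregnancies is high after surgery on patients with deep endometriosis".
- **Missing covariates.** "for regression models requiring complete covariates, complete-case analysis will be applied".
- **Analysis principle.** Statistical Considerations opens by placing all analyses under intention to treat.

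**The concern.** A covariate in a randomised comparison should be fixed before allocation. As recorded, the fertilisation method is not. In the surgery arm it is set after the operation and a recovery delay of two to three months. It can differ between a woman's cycles, and no rule says which cycle counts.

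Some women also have no value at all. A woman who delivers after spontaneous conception following surgery, without ever starting ART, is a success on the primary outcome with no ART type. A woman who withdraws before ART, or whose cycles are all cancelled before oocyte pick-up, is usually a failure with no ART type. The complete-case rule removes both. Exclusion then depends on what happened after randomisation and partly on the outcome, and it can differ by arm, because only the surgery arm has a planned interval between first treatment and ART.

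At stake is the credibility of the adjusted relative risk for the primary endpoint, of the adjusted secondary models that use the same list, and of the IVF/ICSI interaction. The adjusted estimate will be read beside the crude one. If the two differ, a reader could not tell covariate adjustment from selection.

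**Working it through.** **1. The plan's own figure.** The inputs are 55% versus 71%, two-sided α = 0.05 and 80% power (Power Calculation and Sample Size). The pooled-variance formula without continuity correction is

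n = [1.96·√(2·0.63·0.37) + 0.842·√(0.55·0.45 + 0.71·0.29)]² / 0.16² = (1.338 + 0.567)² / 0.0256 ≈ 142 per arm.

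This reproduces the stated 142. The true relative risk (RR) is 0.71/0.55 = 1.29. The calculation is for the unadjusted two-proportion comparison and does not involve ART type.

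**2. Dropping only spontaneous live births in the surgery arm.** Let s be the share of that arm with a spontaneous live birth and no ART. The documents give no value, so s is an assumption shown as a range. Also assumed: the 71% includes these births, nobody in the ART arm is dropped, and the other covariates are balanced among the women who remain.

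Complete-case surgery rate = (0.71 − s)/(1 − s)

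| s | births dropped of 175 | surgery rate | RR against 0.55 |
|---|---|---|---|
| 0 | 0 | 71.0% | 1.29 |
| 5% | 8.75 | 0.66/0.95 = 69.5% | 1.26 |
| 10% | 17.5 | 0.61/0.90 = 67.8% | 1.23 |
| 20% | 35 | 0.51/0.80 = 63.8% | 1.16 |

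A simulation of 400 trials with 175 per arm fitted a modified Poisson model, with IVF/ICSI split evenly and unrelated to outcome. It gave adjusted RRs of 1.24 at s = 10% and 1.17 at s = 20%, in line with the formula.

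**3. Dropping surgery-arm failures as well.** Let d be the share of the surgery arm with neither a birth nor a fertilisation.

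Complete-case surgery rate = (0.71 − s)/(1 − s − d)

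- s = 10%, d = 5%: 0.61/0.85 = 71.8%, RR 1.30
- s = 10%, d = 10%: 0.61/0.80 = 76.3%, RR 1.39

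The two effects cancel when d = (0.29/0.71)·s = 0.41·s, which is 4.1% of the arm at s = 10% and 8.2% at s = 20%. The protocol allows for 20% attrition overall, so d values of this order cannot be ruled out.

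**4. Losses in the ART arm.** If spontaneous live births amounting to 5% of the ART arm are also dropped, its rate becomes 0.50/0.95 = 52.6%. With s = 20% the RR is then 0.6375/0.526 = 1.21, compared with 1.16 in step 2.

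**The case against.** **The primary analysis does not use ART type.** This stands. The headline result is the crude RR, and the planned 80% power belongs to that comparison. A reader might infer that the trial loses power for its primary test. The protocol does not support that, because the exclusion acts only in the adjusted models. The IVF/ICSI subgroup is also labelled exploratory.

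**The bias need not go against surgery.** This stands too. It is tempting to conclude that the model deletes surgery's successes and so understates its effect. That follows only if successes alone are lost. Step 3 shows that modest losses of failures reverse the sign.

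**The size is assumed.** The background says only that spontaneous pregnancies are frequent after surgery for deep endometriosis, without a figure. The 55% and 71% are described as rates after three IVF cycles, so it is unclear whether the 71% includes spontaneous births.

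**ART type could mean something else.** The protocol never states when it is fixed. An intended method, set before randomisation, would avoid the problem. But no such variable is specified, and the only recorded version is the method performed.

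**This could be left to the statistical analysis plan.** Variable derivation often is. Here, however, the protocol itself fixes both the covariate list and the complete-case rule. A separate category for women without ART would not rescue the model, because membership would depend partly on the outcome. The promised sensitivity analyses for missing data do not remove the covariate from the planned model.

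**Conclusion.** The point holds for the adjusted live-birth model, for the adjusted secondary models that use the same covariates, and for the IVF/ICSI subgroup. As written, they condition on a post-randomisation variable and exclude women partly because of their outcome, which conflicts with the protocol's intention-to-treat statement. It does not hold for the crude RR or its power.

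The size and sign of the bias in the adjusted RR cannot be settled from the protocol. Against a true 1.29, the assumed scenarios run from 1.16 (spontaneous births in 20% of the surgery arm dropped, nothing else) to 1.39 (10% spontaneous births plus failures equal to 10% of the arm). They rest on the planned 55% and 71%, on the assumed shares, and on the 71% including spontaneous births.

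This should be fixed, but it does not threaten the headline result.

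**What to change.** Remove ART type from all participant-level adjusted models (live birth, pregnancy and the Cox models) and from the subgroups of the primary outcome. Alternatively, replace it with a variable fixed before randomisation. The male-factor infertility item in the baseline list is already collected and could serve, using the value known before allocation. Keep IVF versus ICSI for per-cycle analyses only.

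The wording changes fall in the definition of the primary outcome measure, Primary analysis, Exploratory subgroup analyses and Covariates. The last should also be reconciled with the EHP-30, EQ-5D and NRS models, which list age, BMI, AMH and center but not ART type.

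The cost is an amendment of wording. No new data are needed for removal or for the male-factor item. Using an intended fertilisation method instead would need one extra item recorded before randomisation.

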**Exploratory subgroup analyses**

Exploratory subgroup analyses will be conducted using treatment-by-subgroup interaction terms in regression models. Subgroups of interest include type of ART (IVF vs ICSI), age (<35 vs ≥35 years), ovarian reserve (AMH categories), and surgical characteristics (adnexal surgery yes/no; anterior vs posterior deep endometriosis, KVÅ codes). These analyses are exploratory and not adjusted for multiplicity.

Secondary endpoints

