- postpartum complications (defined as within 8 weeks postpartum): infections (endometritis, pelvic inflammatory disease, urinary tract infection, wound infection, sepsis), remaining conceptual tissue with and without surgical intervention, use of analgesics

COVARIATES

Potential covariates will be collected from patients’ medical records.

*Baseline characteristics:*

- Age (continuous and dichotomized as < and > 35 years)
- Infertility duration (months)
- Infertility due to social factors (yes/no)
- Infertility due to pain from endometriosis (yes/no)
- Infertility due to male factor (yes/no)
- Smoking (yes/no)
- Snuffing (yes/no)
- BMI (continuous)
- Hormonal endometriosis treatment (yes/no, if yes subtype of drug, duration of hormonal treatment prior to first surgery or ART)
- Parity (0, 1-2 or >2)
- previous caesarian sections (yes/no)
- previous abdominal surgery (yes/no)
- previous adnexal surgery (yes/no)
- previous uterine or cervical surgery (yes/no, type of surgery)
- smoking habits (yes/no)
- ovarian reserve (AMH<0.5ng/L, 0.5-3.5 ng/L and AMH >3.5ng/L)
- myoma (yes/no)
- time from randomization to first oocyte pick-up or surgery (depending on which treatment arm the patient is randomized to)
- ASA-class (1-2 or 3-4)
- Other diseases affecting the outcome: hypothyroidism, diabetes, bleeding disorders or thrombogenic diseases, hypertension, hyperprolactinemia

*Imaging specific data (Ultrasound MRI)*:

- #ENZIAN-score
- AAGL-score
- Adenomyosis (yes/no)
- antral follicle count (AFC)

*Perioperative data:*

- #ENZIAN score
- AAGL score
- EFI score
- Surgical procedure defined by KVÅ- codes: adnexal surgery (yes/no), surgery on deep endometriosis anterior compartment (yes/no) or deep endometriosis posterior compartment (yes/no)
- Colorectal surgery (yes/no, if yes rectal shaving, discoid resection or segmental resection)
- Urological surgery (yes/no, if yes bladder resection, reimplantation of ureter, end to end anastomose of ureter, shaving of ureter)
- Perioperative data: estimated blood loss, operative time, conversion rate
- Annual surgeon volume (number of advanced endometriosis surgeries per year)
- Cumulative surgeon volume (number of advance endometriosis surgeries in total at surgery)
- Consultant surgeon (yes/no, if yes which specialty)
- Reoperation (yes/no) until 2 months post-surgery
- Readmissions (yes/no) until 2 months post-surgery
- Hospital stays (days)
- Time to normal activity of daily life (ADL) (days)

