# STUDY FLOW CHART

# SCHEDULE OF EVENTS TABLE

| Procedures | **Baseline** | **Enrolment** | **1 month prior to surgery or start of first ART cycle^1^** | **Surgery^2^** | **2 months postoperative visit^2^** | **1:st oocyte retrieval** | **2 months after 1:st oocyte retrieval** | **2:nd oocyte retrieval** | **2 months after 2:nd oocyte retrieval** | **3:rd oocyte retrieval** | **2 months after 3:rd oocyte retrieval** | **Visit, phone call or questionnaire 3 years after first treatment (surgery or first ART cykle)** |
| --- | --- | --- | --- | --- | --- | --- | --- | --- | --- | --- | --- | --- |
| **Informed consent oral and written** | x |  |  |  |  |  |  |  |  |  |  |  |
| **Demographics** |  |  | x |  |  |  |  |  |  |  |  |  |
| **Record ultrasound and/or MRI staging according to AAGL and #ENZIAN staging system** | x |  |  |  |  |  |  |  |  |  |  |  |
| **Randomization** |  | x |  |  |  |  |  |  |  |  |  |  |
| **Record surgical procedure according to AAGL and #ENZIAN staging system** |  |  |  | x |  |  |  |  |  |  |  |  |
| **Record intraoperative complications^3^** |  |  |  | x |  |  |  |  |  |  |  |  |
| **Hospital stay** |  |  |  | x |  |  |  |  |  |  |  |  |
| **Record 8 weeks postoperative complications^4^** |  |  |  |  | x |  |  |  |  |  |  |  |
| **EHP-30, EQ5D and NRS scale^5^** |  |  | x |  | x | x | x | x | x | x | x | x |
| **Primary outcome (CLBR)** |  |  |  |  |  |  |  |  |  |  |  | x |
| **Secondary outcome/IVF cycle^6^** |  |  |  |  |  |  | x | x | x | x | x | x |

^1^ start of FSH injections ^2^only first line surgery group ^3^According to Classic ^4^According to Clavien Dindo ^5^Endometriosis Health Profile and Numeric Rating Scale ^6^LBR, PR, number of oocytes retrieved, fertilization grade, number of blastocysts

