# STUDY ENROLLMENT

SCREENING PROCEDURE AND PARTICIPANT IDENTIFICATION

All women with stage III-IV AAGL endometriosis with infertility referred and/or eligible for surgery and/or ART-treatment such as IVF or ICSI will undergo screening for this trial. The results of this screening will be documented in a screening log. After obtaining oral and written informed consent, patients will be registered and randomized. Registration data will be entered to an electronic Case Report Form (eCRF).

STAGING

At baseline, a specialized transvaginal and abdominal ultrasound examination, supplemented with transabdominal ultrasound if indicated will be performed according to the International Deep Endometriosis Analysis (IDEA) group recommendations (25) to identify endometriosis lesions. Ultrasound and, if needed, magnetic resonance imaging (MRI) findings will be classified using the #ENZIAN and AAGL classification system (4, 6)**.**

The presence of adenomyosis will also be documented and characterized according to the Morphological Uterus Sonographic Assessment (MUSA) group recommendation (26, 27) . Women with and without suspected adenomyosis will receive the same treatment protocols. Presence of adenomyosis will not influence allocation but will be considered during the discussion of the final analysis of study results.

The use of hormonal treatment for endometriosis, prior to the surgery/ first ART-treatment or between the surgery and ART-treatment, will be documented and considered in the discussion of the outcomes.

INCLUSION CRITERIA

- Age 18 - 38 years old
- Endometriosis AAGL stage III-IV
- Referred or eligible for ART-treatment such as IVF or ICSI, independent of infertility diagnosis (28) (including sperm donation cycles for social reasons) and/or infertility due to dyspareunia/dysmenorrhea caused by endometriosis
- Body mass index 18-35 kg/m^2^
- Patients who have signed an approved Informed Consent

EXCLUSION CRITERIA

- Previous surgery for endometriosis except diagnostic laparoscopy.
- Previous IVF/ICSI-cycles (including prior fertility preservation cycles)
- Hemato- and/or hydrosalpinx
- Clear indication for surgery such as ureteral stenosis or intestinal sub-occlusive symptoms
- Suspicion of malignancy
- Submucosal fibroids (The International Federation of Gynecology and Obstetrics (FIGO) 0-1, any size) or intramural fibroids (FIGO 2-5, > 4 cm largest diameter of the largest myoma) (29)

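### The surgical subgroups are defined by procedures performed after randomisation, so the planned treatment-by-subgroup interactions have no valid comparator in the ART arm

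*Protocol*

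**What the plan says.** Under Statistical Considerations, the Protocol states that exploratory subgroup analyses "will be conducted using treatment-by-subgroup interaction terms in regression models". Among the subgroups it names "surgical characteristics (adnexal surgery yes/no; anterior vs posterior deep endometriosis, KVÅ codes".

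The Definition of primary outcome measure (Study Objectives) lists the pre-specified subgroups for the primary outcome. They include "adnexal surgery (yes/no), surgery on deep endometriosis anterior compartment (yes/no) or deep endometriosis posterior compartment (yes/no", and the text refers to the KVÅ classification of surgery for their definition.

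The Covariates list places the same item among the perioperative data, not the baseline characteristics: "Surgical procedure defined by KVÅ- codes: adnexal surgery (yes/no". The KVÅ lists in the Appendix contain operations such as cyst enucleation, bowel resection and bladder resection. They do not list lesions.

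In the Schedule of Events Table, the footnote on the surgery column reads "only first line surgery group". The control treatment is first-line ART.

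Under Staging, imaging is done at baseline and "findings will be classified using the #ENZIAN and AAGL classification system". The schedule puts this record in the baseline column, ahead of the enrolment column that holds randomisation.

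**The concern.** A treatment-by-subgroup interaction asks whether the effect of allocation differs between types of women. Both arms must then contain women of each type, and type must be fixed before allocation. Neither condition is met here. Whether a woman counts as having had adnexal, anterior or posterior surgery depends on an operation that the plan gives only to the surgery arm.

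Within the surgery arm, membership also depends on decisions and events after allocation. The Surgical Procedure section tailors technique to the patient and considers gentler methods where ovarian reserve is already reduced, so the procedure can depend on a prognostic factor. The anterior list includes suture of the bladder and ureter, and the same part of the Protocol names bladder and ureteral injury as complications, so repair of an operative injury could place a woman in a subgroup. Under intention to treat, surgery-arm women who are never operated on become a no, which mixes non-adherence with anatomy.

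At stake is a result that either cannot be computed or is a non-randomised contrast reported as a pre-specified interaction.

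**Working it through.** **Inputs.** Planned total 350 with 1:1 allocation, so 350 / 2 = 175 per arm. Assumed cumulative live birth rates are 55% (ART) and 71% (surgery plus ART), from Power Calculation and Sample Size. The Protocol gives no figure for any interaction. Subgroup prevalence and the rate of later surgery in the ART arm are not given either, so both are assumed below.

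**The plan's own figure, for context.** Two-sided α = 0.05, 80% power, pooled variance, mean proportion 0.63:

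n = [1.960·√(2·0.63·0.37) + 0.842·√(0.55·0.45 + 0.71·0.29)]² / 0.16² ≈ 141.8, i.e. 142 per arm.

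This reproduces the stated 142. The point below does not depend on it.

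**1. Is the interaction identified?** Let T = 1 for the surgery arm and S = 1 for having the procedure. On the log scale the interaction is

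[log p(T=1,S=1) − log p(T=0,S=1)] − [log p(T=1,S=0) − log p(T=0,S=0)].

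If no ART-arm woman is operated on, S = 0 whenever T = 0. Then S = T×S for every woman and the cell T=0, S=1 is empty.

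- Columns [1, T, S, T×S], 175 per arm: rank 3 of 4.
- All three yes/no variables from the Definition of primary outcome measure entered together, with their interactions: rank 5 of 8.

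If software drops the redundant column, the surviving coefficient is log p(T=1,S=1) − log p(T=1,S=0). That compares women within the surgery arm and is not an interaction. A larger sample would not help.

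For the item worded as anterior versus posterior there is not even a no level to fall back on. An ART-arm woman without an operation has no procedure-based value.

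**2. What if some ART-arm women are operated on later?** Assume 2% to 10% are, half of them with S = 1, and that the surgery arm splits 88/87. Each cell contributes (1 − p)/(n·p) to the variance of the log ratio of relative risks.

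- 2%: ART cells 2 and 173. Variance = 0.4085·(1/88 + 1/87) + 0.8182·(1/2 + 1/173) = 0.0093 + 0.4138 = 0.4232; SE 0.65.
- 5%: 4 women with S = 1; SE 0.47.
- 10%: ART cells 9 and 166. Variance = 0.0093 + 0.0958 = 0.1052; SE 0.32.

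The multipliers are 0.29/0.71 = 0.4085 and 0.45/0.55 = 0.8182. The term is now estimable, but the ART-arm yes group is about 2 to 9 women chosen by events after randomisation.

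**3. What would baseline imaging subgroups give?** S is then defined in both arms and the matrix has rank 4 of 4. Apply the planned rates in both subgroups.

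- 50% prevalence: SE = √[(0.4085 + 0.8182)·(1/87.5 + 1/87.5)] = 0.167. Ratio of relative risks detectable with 80% power: exp(2.802·0.167) ≈ 1.60.
- 30% or 70% prevalence: SE = √[1.2266·(1/52.5 + 1/122.5)] = 0.183; detectable ratio exp(2.802·0.183) ≈ 1.67.

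For scale, the planned overall relative risk is 0.71/0.55 = 1.29.

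**The case against.** **A reader might infer that the ART-arm yes cell is exactly zero, so the interaction can never be estimated.** The Protocol does not support that. It compares first-line strategies over three years, analyses by randomised group, foresees as-treated analyses, and nowhere forbids later surgery in the ART arm. Exact non-identification is conditional on no such surgery. What stands without that condition is that membership is decided after randomisation.

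**A reader might also infer that three interactions are planned.** The section that specifies interaction terms names two surgical items. The three yes/no variables come from the Definition of primary outcome measure, which mentions no interaction.

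**The wording could mean lesion location.** Taken alone, the phrase anterior versus posterior deep endometriosis names disease. But it carries the KVÅ tag, and two other sections describe surgery performed. The baseline item on previous adnexal surgery is a separate covariate and does not supply the missing comparator.

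**The sponsor may have wanted results by procedure.** That is possible, since the Protocol does not give its reason for these subgroups. Results by procedure remain available descriptively within the surgery arm, but they cannot be obtained as an interaction with allocation.

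**The analyses are exploratory and a statistical analysis plan could repair them.** The first part is true and limits the severity. On the second, this is not a detail left open: the Protocol fixes both the variable and the model, and the two do not fit together.

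**Conclusion.** The point holds. As defined, the surgical subgroups cannot support a valid treatment-by-subgroup interaction. With no later surgery in the ART arm the interaction is not identified. With 2% to 10% later surgery it is computable, with a standard error of about 0.65 to 0.32 on the log scale, but on a small self-selected group.

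This rests on reading the variables as procedures performed, which the KVÅ definition and the perioperative listing support. The rates of later surgery are assumptions.

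It should be fixed, but it is not critical. It touches only analyses labelled exploratory. The primary intention-to-treat comparison, sample size, randomisation and safety monitoring are unaffected, and the Protocol gives no ground for a wider conclusion.

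**What to change.** Change the Definition of primary outcome measure and the Exploratory subgroup analyses so that they name the same variables. Take these from the baseline ultrasound/MRI #ENZIAN/AAGL record for all women, for example ovarian endometrioma (yes/no), anterior deep endometriosis (yes/no) and posterior deep endometriosis (yes/no), and test those interactions. State that results by KVÅ procedure are descriptive and confined to the surgery arm.

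The cost is wording in two sections, since the imaging data are already collected before randomisation in both arms. Because the trial is open label, the change is best made before outcomes accrue.

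There is a downside. Imaging subgroups ask about lesion location, not procedure, and do not map exactly to the KVÅ lists: the adnexal list includes salpingectomy and ovariolysis, the posterior list appendectomy and small-bowel resection, and the anterior list parametrial excision. With a detectable ratio of relative risks of about 1.6 to 1.7 at the assumed prevalences, only large differences would show, so these analyses should stay labelled exploratory.
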